## Abstract

**Background:**

The incidence of biliary complications following liver transplantation (LT) remains high, ranging from 10 to 50 % of patients, especially when the diameter of the bile duct is smaller than 7 mm. Biliary reconstruction is most often performed by duct-to-duct anastomosis. In a preliminary study (n = 20), we previously reported a technique of biliary reconstruction using an intraductal stent tube followed by its endoscopic removal and showed both the feasibility and safety of this innovative procedure. The next step is to validate the potential benefit of this procedure in a randomized controlled trial.

**Design:**

This is a multicenter randomized controlled trial in France comparing the efficacy of biliary reconstruction with or without a removable intraductal stent on reducing biliary complications. Inclusion and randomization are performed during LT when a duct-to-duct biliary anastomosis smaller than 7 mm in diameter is envisioned. In the intraductal stent group, a custom-made segment of a T-tube is placed into the bile duct and removed endoscopically 4 to 6 months later. The surgical technique is described in a video during randomization and is available on the secure website used for inclusion and randomization. The primary endpoint is the occurrence of biliary complications, including biliary fistulae and strictures, during the 6 months of follow-up. Secondary evaluation criteria are the incidence of complications related to the stent placement and its extraction by endoscopy. The inclusion of 248 patients in total has been determined based on an expected incidence of biliary complications of 25 % in the non-IST group and a 60 % reduction of biliary complications (10 %) in the IST group.

**Discussion:**

Biliary complications following LT are significant causes of morbidity, retransplantation, and mortality. Although controversial, the use of a T-tube has been proven to be useless and even responsible for specific complications related to the external part of the tube in many studies, including several randomized trials. However, several studies have identified a small bile duct diameter as a risk factor for biliary stenosis. A threshold of 7 mm was found to be significantly associated with biliary stenosis. Our team published a preliminary study that included 20 patients using a new technique of intraductal stenting. Only four complications were reported in the overall study population, whereas no biliary complication occurred in the subgroup of patients who received a whole graft LT. Moreover, no technical failures and no procedure-related complications were noted before and during the drain removal. Although an intraductal stent tube in duct-to duct biliary anastomosis seems feasible and safe, a multicenter randomized controlled trial is needed to validate its benefit as a protective tool against the occurrence of biliary complications. One original aspect of this protocol is the video demonstration of the surgical procedure, which is available on the web to standardize and homogenize the technique. The surgical community may be inspired by this type of tool in the future to minimize technical bias related to technical issues.

**Trial registration:**

NCT02356939, date of registration 2 February 2015.

## Background

Biliary tract reconstruction during liver transplantation (LT) is the final technical step and the cornerstone of the procedure and is often performed by a duct-to-duct anastomosis. Rarely, recipient and donor biliary stump discrepancies or liver disease-related reasons could lead to a hepaticojejunostomy. The proper completion of this technical step is crucial for postoperative outcome [1, 2]. The incidence of biliary complications following liver transplantation (LT) remains high, ranging from 10 to 50 % of patients among clinical series despite an increasing experience worldwide [2–4]. These complications, mainly represented by biliary leaks and biliary strictures, are responsible for substantial post-transplantation morbidity and graft loss. Biliary leakage occurs mostly within 3 months postoperatively. This early complication reaches a 10 to 20 % incidence rate [3, 4]. Biliary strictures mainly occur later, within 5 to 8 months and up to 1 year in most. The reported incidence of biliary strictures still ranges from 5 to 30 % among large and recent clinical series [2, 4].

The use of an external T-tube to reduce biliary complications has been debated for decades [5–10]. The initial rationale was to facilitate biliary healing and maintain easy access to the biliary tract to perform a cholangiography until removal of the T-tube in consultation, in general within 6 weeks post-transplantation [11]. However, specific complications related to the cholangiography, such as cholangitis, and the development of endoscopic techniques, have reduced its legitimacy. Moreover, numerous published studies [5–8, 10], including three randomized studies [6–8], have shown not only an absence of difference of biliary complications with or without the T-tube use but also a specific morbidity related to the T-tube, such as cholangitis, and biliary leaks at the time of removal.

Those results have been criticized by two randomized studies [9, 12]. However, in one of these [9], the biliary strictures rate was similar between the T-tube and the non-T-tube group, and a higher general biliary complication rate (50 %) depended on an increased 14 % rate of pancreatitis. In the second study, which showed increased biliary strictures in the non-T-tube group in a monocentric design [12], the general biliary complications rate was similar, with a diagnosis of biliary stricture exclusively based on size discrepancy on imaging. The rate of Kehr-related complications was 23 % (13 % fistulae). The principal interest of this latter study was the significantly increased risk of biliary stricture in patients with bile duct size < 7 mm.

Based on these results, numerous teams do not use an external biliary drain in LT anymore. Moreover, the efficacy and safety of endoscopic biliary stenting has been highlighted in several studies in the treatment of biliary stenosis [13–17].

In this context, we developed a new technique of intraductal stent tube (IST) placement followed by its endoscopic removal in the 4 to 6 months postoperatively. The rationale was to prevent the biliary complications while avoiding the side effects related to an external T-tube use. We published a preliminary study conducted on 20 patients with a small graft bile duct (<5 mm) [18]. Biliary complications occurred in four patients, including one cholangitis, one hemobilia, one asymptomatic leakage, and one anastomotic stricture. No biliary complication occurred in the subgroup of patients who received a whole graft LT. No technical failure and no procedure-related complication were recorded during drain removal. Given the so–reported feasibility and safety of this innovative technique, we sought to evaluate its impact on biliary complications prevention.

The primary goal of this multicenter, randomized controlled study is to determine the incidence of biliary complications in the IST group, especially in case of small bile duct reconstruction, compared to the standard technique (duct-to-duct biliary reconstruction without IST) within the first 6 months post-liver transplantation. The second endpoint is to compare the incidence of complications related to the stent tube and its extraction by endoscopy.

## Methods

### Goals and outcomes

This multicenter randomized controlled study aims at comparing the efficacy of biliary intraductal stent tube placement in biliary end-to-end anastomosis to the standard technique (duct-to-duct biliary reconstruction without IST) on the incidence of biliary complications, that is, biliary strictures and biliary stenosis, within the first 6 months post-liver transplantation.

The primary outcome is the incidence of biliary strictures and biliary leakage within 6 months post-transplantation.

A biliary leakage was defined according to the ISGLS classification [19] as a bilirubin concentration in the drain fluid at least three times the serum bilirubin concentration on or after postoperative day 3 or as the need for radiologic or operative intervention resulting from biliary collections or bile peritonitis. A Grade A bile leakage caused no change in the patients' clinical management. A Grade B bile leakage required active therapeutic intervention but was manageable without relaparotomy, whereas in Grade C, bile leakage relaparotomy was required.

A biliary stenosis was defined by a size discrepancy between the two sides of the bile duct anastomosis on specific imaging (MR cholangiography or ERCP), associated with an upstream bile tract distention, with a clinical and biological cholestasis (gamma-glutamyl transferase and alkaline phosphatase three-fold elevation from baseline associated with an abnormal bilirubin serum level within 2 days), after excluding other cholestasis causes (rejection and viral reactivation).

Secondary endpoints are the incidence of specific complications related to the IST and its extraction by endoscopy: cholangitis, stent migration, extraction difficulties, acute pancreatitis, digestive perforation, and hemorrhage. The graft and patients’ survival at 6 months will also be analyzed as secondary endpoints.

### Patient selection

Patient inclusion is performed in consultation at the time of enlistment for LT, where they are informed and have to sign a written consent.

Inclusion criteria are as follows:Adults older than 18 years-old.Patients eligible for a liver transplantation.Patients’ written informed consent signed.

Exclusion criteria include the following:Biliary reconstruction requires a hepaticojejunostomy for anatomical/biliary disease reason.Ineligibility for liver transplantation.

Definitive inclusion takes place in the operating room, during LT, and depends on the fulfillment of the following “definitive inclusion criteria”:Duct-to-duct, end-to end biliary reconstruction.Graft or recipient biliary duct diameter ≤ 7 mm.Anatomically entire graft choledoque.No graft from a circulatory arrested donor.

### Study course

The study is a multicenter, prospective, randomized controlled study. The follow-up is set at 6 months postoperatively to screen the majority of biliary complications. The inclusion period is set at 2 years, for a total study duration of 2.5 years.

The patient inclusion will be made in seven liver transplantation centers in France.

Definitive inclusion will take place in the operating room, during LT, and depends on fulfillment of the indicated “definitive inclusion criteria” (see above).

The randomization will be performed in the operating room by the investigator and coordinated by the Clinical Research Unit of the promoters’ center (Saint Antoine Hospital, Paris), with specific software accessible on the Internet.

In the IST group, the surgeon will place the IST in the bile duct, which is a custom-made segment (2 cm) of an 8 Charrière T-tube. The stent is inserted in the biliary duct without suture fixation (Fig. 1).

**Fig. 1 Fig1:**
[figure not shown]
Intraductal stent tube insertion (short movie extracts)

To minimize bias and homogenize the technique, a short technical explanatory movie was developed by the principal investigator’s team and provided on the internet. The technique of biliary reconstruction by either running suture or interrupted stiches is left to the surgeon preference because no impact has been demonstrated on the occurrence of biliary complications.

Each center performs its habitual postoperative follow-up. Clinical, biological, and radiological data are collected at Day 1, Day 7, Day 15, Month 1, Month 3, and Month 6. A Magnetic Resonance Cholangiography (MRC) is performed at 6 months post-LT, which is after the stent removal.

In the IST group, an endoscopic retrograde cholangio-pancreatography (ERCP) with sphincterotomy is planned between the 4^th^ and the 6^th^ month post-transplantation, requiring a short stay in the hospital, a general anesthesia, and clinical and biological tests including plasmatic lipase dosage at Day 1.

Every undesirable event will be immediately reported to the sponsor for further investigation of its severity. Severe undesirable events are previously defined.

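### Follow-up ends at month 6, when the stent-removal window closes, so scheduled observation after extraction varies from about 61 days to none

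*Protocol article*

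**What the plan says.** The Abstract (Design) says the stent segment is "placed into the bile duct and removed endoscopically 4 to 6 months later". Methods, Study course puts the ERCP with sphincterotomy in the same window, with a short hospital stay and "clinical and biological tests including plasmatic lipase dosage at Day 1".

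The same section states: "The follow-up is set at 6 months postoperatively". With two years of inclusion and 2.5 years in total, the last patient has exactly 6 months. The MR cholangiography (MRC) "is performed at 6 months post-LT, which is after the stent removal".

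On data capture, "data are collected at Day 1, Day 7, Day 15, Month 1, Month 3, and Month 6", so no visit is listed between Month 3 and Month 6. Two provisions run alongside: "Each center performs its habitual postoperative follow-up", and "Every undesirable event will be immediately reported to the sponsor", the latter with no stated end date.

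Methods, Goals and outcomes makes the "incidence of specific complications related to the IST and its extraction by endoscopy" a secondary endpoint. Its components are cholangitis, migration of the stent, difficult extraction, pancreatitis, perforation and bleeding. The period over which they count is not tied to the date of removal.

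**The concern.** The removal window and follow-up close on the same date. Following the schedule exactly, a patient whose stent comes out at month 4 is observed for two months afterwards, and one whose stent comes out at month 6 for no scheduled time beyond the ERCP stay and its Day 1 tests. Nothing clinical need separate the two patients; the difference can come purely from when the ERCP was booked.

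The extraction-complication rate informs whether any benefit of the stent is worth a second procedure under general anesthesia. With few events expected, one or two missed ones would be a visible share of the rate. A rate built on unequal periods is also harder to compare between patients or centers. The exposed component is mainly cholangitis, which can appear after discharge.

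**Working it through.** The article gives no figure for post-removal observation, so there is none to reproduce. The check uses its dates.

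**Inputs from the article**
- Removal window: months 4 to 6 (Abstract, Design; Methods, Study course).
- End of follow-up: month 6 (Methods, Study course).
- Total sample size: 248 (Methods, Statistical analysis).
- Cited ERCP complication rates: about 4 % overall, with pancreatitis 2 to 3 % and hemorrhage 0.3 % (Discussion).

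**Assumptions**
- Equal allocation, so 248 / 2 = 124 stent patients, all with endoscopic removal.
- Removal dates spread evenly over the window.
- A month of 30.44 days.
- A 30-day period of interest after removal.
- No event captured after month 6. This is the least favorable case.

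**Step 1. Time left after removal** = (6 − month of removal) × 30.44 days.

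| Removal at month | Days to end of follow-up |
|---|---|
| 4 | 60.9 |
| 4.5 | 45.7 |
| 5 | 30.4 |
| 5.5 | 15.2 |
| 6 | 0 |

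**Step 2. Expected events** = 124 × 0.04 = 4.96, about 5.

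**Step 3. Share falling past month 6.** If events are even over 30 days, the mean delay is 15 days. With removal dates even over 60.9 days, the share past month 6 is 15 / 60.9 = 24.6 %.

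**Step 4. Events past month 6**, by the proportion already seen by Day 1:

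| Seen by Day 1 | Calculation | Events missed, of about 5 |
|---|---|---|
| None | 4.96 × 0.246 | 1.2 |
| 50 % | 0.5 × 1.22 | 0.6 |
| 80 % | 0.2 × 1.22 | 0.2 |

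The 50 % and 80 % splits are assumptions. The cited rates fit them: pancreatitis plus hemorrhage come to (2 + 0.3) / 4 = 58 % up to (3 + 0.3) / 4 = 83 % of the overall rate, if the categories do not overlap and both show early.

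**Step 5. Sensitivity to timing.** If every removal took place by month 5, at least 30.4 days would remain and a 30-day count would lose nothing. If every removal fell evenly between months 5 and 6, the share in Step 3 would double to 15 / 30.44 = 49.3 %, giving 0.5 to 2.4 events.

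**Step 6. Patients whose 30-day period passes month 6** = 124 × 30 / 60.9 = 61.1, about 61.

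**The case against.** The strongest reply is that the loss is assumed rather than shown. The article nowhere says that capture stops at month 6: events are reported immediately with no end date, and centers keep to their habitual follow-up. Any patient whose stent is removed before month 6 still has the Month 6 visit. Most of the listed components also depend little on later observation. Difficult extraction is seen during the procedure, migration concerns a stent still in place, and pancreatitis is looked for at Day 1. All of this stands, and it is why the lower figures are the more likely ones. It does not remove the point: scheduled follow-up is still set at 6 months, later capture is not guaranteed, and cholangitis is a listed component.

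A second reply is that removals near or after month 6 may be rare. The Discussion mentions removals beyond 6 months in the team's earlier experience. That shows they happen, but not how often they would here.

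A reader might infer two stronger things.
- **That the plan allows the MRC to be read with the stent in place.** The document does not support this: Study course states that imaging follows removal. A minimum interval or a rule for late removals is detail that an article may leave to the full protocol.
- **That the primary endpoint is biased**, because strictures are described as appearing mainly at 5 to 8 months. The primary outcome is counted over the same 6 months from transplantation in both arms. The overlap of dates described here does not show that it is measured wrongly.

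**Conclusion.** The point holds in a limited form. As scheduled, observation after extraction runs from about 61 days to about 0, according to the ERCP date, so later complications after a late removal may be missed. Only the stent arm is concerned, and only one secondary endpoint.

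The size is about 0.2 to 1.2 of about 5 expected events, with the lower end more likely. This rests on 124 stent patients, even timing, a 4 % rate and no capture after month 6. Late-clustered bookings would raise it; habitual follow-up and immediate reporting would lower it. Sample size and the primary endpoint are unaffected. This is a cheap improvement the sponsor could make, not a fault that threatens the trial's main conclusion.

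**What to change.** Count extraction complications over a fixed 30 days after every removal, whatever its date. Where the 30 days pass month 6, complete the record by telephone or from the hospital notes. Record also whether the stent was in place at the month-6 MRC, which documents that the stated order was kept.

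The cost is one contact or record check in about 61 of an assumed 124 stent patients. Contact with the last patient extends by up to about 30 days, or longer if that removal is itself delayed past month 6. No extra imaging is needed, and the removal window, the stenting time and the 6-month primary endpoint stay as they are. The 30 days is a proposed convention, not a figure from the article; another fixed period would serve if it is the same for all patients.

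A mandatory gap between removal and imaging is not proposed. The order is already stated, and a gap would shorten stenting, whose longer duration the Discussion presents as an advantage of the technique.

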### Statistical analysis

The inclusion of 248 patients in total has been estimated based on an expected incidence of biliary complications of 25 % in the non-IST group, and a 60 % reduction of biliary complications (10 %) in the IST group with an alpha risk of 5 % and a beta risk of 20 %.

The statistical analysis will be in an intention-to-treat fashion. The frequency of occurrence of a biliary complication will be compared between groups with a χ^2^ test or a Fisher test as appropriate.

Adjusting factors such as arterial thrombosis or surgical technique will be managed with logistic regression models as appropriate.

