Some complications specific to the stent may also be expected, such as stent migration in the duodenum, infectious cholangitis, or extraction difficulties due to stent incrustation. In our experience, one cholangitis occurred and was successfully treated by antibiotics and drain removal. This latter patient had a transpapillary drain that may explain the occurrence of a backflow into the biliary tract [18]. Consequently, we decided to systematically place the tube above the ampulla of Vater. One patient experienced a clinical asymptomatic spontaneous migration of the stent in the duodenum, without any consequences. No difficulties were recorded during IST ablation because of stent incrustation, event after more than a 6-month postoperative delay.

We previously performed this technique in patients with a graft bile duct diameter less than 5 mm. This option was based on several studies [12, 21–23] that demonstrated a significant association between the risk of biliary stenosis and the small diameter of the biliary duct. Asian studies [21–23] found a significantly increased risk for less than 5 mm bile duct diameter, but these studies are conducted on reduced liver grafts obtained from living donors. A recent trial [12] found a significantly increased risk for bile ducts less than 7 mm in diameter in 197 transplanted patients from whole cadaveric liver grafts. Thus, a cut-off value of 7 mm for graft bile duct diameter was chosen for this trial.

In the design of this trial, we assumed an expected biliary complication rate in the non-IST group of 25 %. We considered that these patients with a small bile duct diameter (<7 mm) presented a higher risk of biliary strictures, according to the literature. A 60 % reduction in biliary complications, representing a 10 % biliary complication rate in the IST group, seemed to be a reasonable goal.

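### The primary comparison is a crude chi-square or Fisher test that leaves out bile duct diameter, the article's own main risk factor assessed before randomisation: a modest loss of efficiency

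*Protocol article*

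**What the plan says.** All places are in the protocol article.

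- **Statistical analysis.** The analysis is by intention to treat. "The frequency of occurrence of a biliary complication will be compared between groups with a" chi-square or Fisher test. The next sentence reads "Adjusting factors such as arterial thrombosis or surgical technique will be managed with logistic regression models as appropriate". It does not say whether such a model would be primary or supportive, and it names neither diameter nor centre.
- **Patient selection.** The criteria checked in the operating room include "Graft or recipient biliary duct diameter" of at most 7 mm. Under Study course, this check and the randomisation both take place in theatre, and definitive inclusion depends on the check. Diameter is therefore a baseline variable.
- **Discussion.** The earlier, narrower cut-off of 5 mm is justified by studies that "demonstrated a significant association between the risk of biliary stenosis and the small diameter of the biliary duct". The 7 mm limit and the assumed 25 % control rate are both defended by the extra risk in small ducts.
- **Study course.** "The patient inclusion will be made in seven liver transplantation centers in France". The article says nothing on whether randomisation is stratified.

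**The concern.** A covariate that is known before allocation and predicts the outcome can be put in the primary model without harming validity. Doing so removes the part of the outcome variation that it explains, and it corrects for chance imbalance between the arms. The article presents small duct diameter as the reason these patients are at high risk, yet its stated group comparison ignores how small the duct is. The covariates that it does name are not the baseline factor on which its rationale rests.

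At stake is some precision in a trial that expects few events, and a primary estimate that would carry any chance imbalance in diameter. The validity of the test is not at stake.

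**Working it through.** **Inputs from the Statistical analysis section.** "The inclusion of 248 patients in total has been estimated based on an expected incidence of biliary complications of 25" % in the control arm, "a 60 % reduction of biliary complications (10 %) in the IST group", "with an alpha risk of 5 % and a beta risk of 20" %. A two-sided test and 1:1 allocation (124 per arm) are assumed, because neither is stated.

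**Step 1: the plan's own figure.** With p0 = 0.25, p1 = 0.10 and mean 0.175, the pooled formula is

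n per arm = [1.960 × √(2 × 0.175 × 0.825) + 0.842 × √(0.25 × 0.75 + 0.10 × 0.90)]² / 0.15²
= (1.053 + 0.443)² / 0.0225 ≈ 99.5, so 100 per arm and 200 in total.

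With a continuity correction the total is 226. The stated 248 is not reproduced from the stated inputs. An unstated allowance for losses would come close, for example 200 / (1 − 0.20) = 250. This gap is on the safe side and is not part of the present point.

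**Step 2: power of the crude test at 124 per arm.**

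Φ[(0.15 × √124 − 1.053) / 0.527] = Φ(1.17) = 87.9 %.

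The exact Fisher test has 85.1 %. Both exceed the 80 % target.

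**Step 3: expected events.** 124 × 0.25 + 124 × 0.10 = 31 + 12.4 = 43.4.

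**Step 4: what adjustment for diameter would add.** The article gives no strength of association within the eligible range, so a range has to be assumed: diameter uniform on 3 to 7 mm, odds ratio 1 to 2 per mm narrower, marginal risks held at 25 % and 10 %. The adjusted test is the likelihood-ratio test for arm in a logistic model. The standardised risk difference is the mean predicted risk over all patients without the stent minus the mean with it.

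Simulation with diameter as the only covariate (6,000 replicates per scenario):

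- Odds ratio 1 (diameter not prognostic): variance ratio, adjusted to crude, 1.00. Essentially nothing is lost.
- Odds ratios 1.25 to 2: power gain of 0 to 2 points and up to 7 % less variance.
- Type I error: 4.9 to 5.2 %.

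A 7 % cut in variance at the top of the range means that 248 × 0.93 ≈ 231 adjusted patients would give the precision of 248 unadjusted ones.

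**Step 5: what centre would add.** A second simulation (3,000 replicates) also gave the seven centres different baseline risks and fitted six fixed centre terms. The last column compares diameter plus centre with the crude analysis.

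| Odds ratio per mm narrower / SD of centre log-odds | Chi-square power | + diameter | + diameter and centre | Variance ratio |
|---|---|---|---|---|
| 1.0 / 0 | 89.6 % | 89.6 % | 89.3 % | 1.03 |
| 1.25 / 0.2 | 89.9 % | 90.1 % | 89.9 % | 1.01 |
| 1.5 / 0.3 | 89.0 % | 89.5 % | 89.2 % | 0.99 |
| 2.0 / 0.5 | 88.7 % | 90.5 % | 91.2 % | 0.92 |

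Under the null (1.5 / 0.3, both arms 25 %), type I error was 5.4 % for chi-square, 5.7 % with diameter and 6.0 % with diameter and centre. The Monte Carlo standard error is √(0.05 × 0.95 / 3000) ≈ 0.4 points. In these runs diameter alone never loses power. Fixed centre terms add to the gain only under the strongest assumptions, and there is a hint of inflated type I error.

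**The case against.** The strongest reply is that nothing here is wrong. An unadjusted test is valid under randomisation, a condensed article need not list every covariate, and the sentence after the test already provides for logistic regression with an open list of examples. The validity point stands in full. The other two stand in part: the article does more than stay silent, because it fixes a crude comparison and names example covariates that leave out its main risk factor.

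It can also be said that the value of diameter within the eligible range is unproven. The 7 mm finding contrasts ducts below and above the limit that eligibility applies. The 5 mm findings come from reduced living-donor grafts, which the Discussion itself sets apart. The association is cited mainly for stenosis, while the endpoint also counts leakage. This stands, and it is why the gain is given as a range that starts at zero. It is softened by two details: eligibility needs only the graft or the recipient duct to be small, so the other may exceed 7 mm, and the Abstract links small ducts to biliary complications in general.

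Four stronger readings are tempting, and the article does not support them:

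- *The precision is free.* The gain may be nil, and the model needs a diameter in mm, whereas eligibility needs only a threshold check.
- *Imbalance could not be corrected.* The logistic regression sentence gives a route, although its covariates and role are left open.
- *Centre belongs in the primary model.* The article offers no evidence that centre is prognostic. Habitual follow-up differs by centre, but that alone does not show a difference in risk.
- *Each centre has its own suture technique.* The Study course section leaves this to the surgeon and regards it as without effect on complications.

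**Conclusion.** The point holds as a modest matter of efficiency. The primary comparison omits a covariate that is assessed before randomisation and that the article treats as its main risk factor. Adjusting for it would change power by about 0 to 2 points and reduce the variance of the risk difference by about 0 to 7 %, with type I error near 5 % and essentially no loss if diameter turns out not to matter.

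These sizes rest on assumptions that the article does not supply: 1:1 allocation, a two-sided 5 % test, diameters uniform on 3 to 7 mm, and odds ratios of 1 to 2 per mm narrower. A reader might infer that the planned test is biased or that the trial is underpowered without adjustment. Neither follows, since the crude test is valid and has 85 to 88 % power at the stated rates with 124 per arm.

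**What to change.** Make the primary analysis a logistic regression of leak or stenosis by month 6 on arm and bile duct diameter, with these details:

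- Diameter is measured in theatre before randomisation and entered as a continuous variable in mm.
- One definition is prespecified, for example the smaller of the graft and recipient ducts. This is needed because Patient selection refers to either duct, while the Discussion speaks of the graft duct.
- The standardised risk difference is reported with its 95 % CI.
- The chi-square or Fisher test is kept as a sensitivity analysis.
- Six fixed centre terms stay out of the primary model, given about 43 expected events. Centre enters only if randomisation is stratified by it, or in a sensitivity analysis.

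The cost is a paragraph of analysis text, some reliance on a model, and a case report form that records the diameter in mm and not only that the 7 mm limit was met. No extra patients are needed.
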